## Discussion

### Summary

During the trial period, the Web app is only available to research participants; therefore, source coding and App content have been preserved.

### Limitations

First, the study relies on an assumed independence of the groups. This means that young participants randomly assigned to 1 of the intervention groups will not share information with those falling in the control group. However, it can happen that some controls have friends assigned to the game or Web app directly and that they visit it with them. This can generate a classification bias, underestimating the real effect of the intervention. Second, information bias to assess primary transmission can occur when not all expected partners to be notified are the ones who visit health centers for testing. Third, those partners receiving a notification but visiting a health center out of the study area will be lost to follow-up if they are assigned to the control group. This will generate a participation bias, overestimating the partner notification yield of the other arms of the study. Fourth, a malicious use of the Web app could occur, when anonymous partner notification is sent by some youngsters to other youngsters who were not even exposed. This may generate overestimation of the partner notification yield. Finally, we cannot fully ascertain the network across experimental conditions because of the anonymous condition of our experiment. It may happen, although very rarely, that partners receive a notification from 2 index cases assigned to different arms of the trial. In that case, the system assumes that the first notification received by the youngster is the one that will be followed-up and the one that will contribute to network analysis.

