### Development of an App to Promote Patient Referral Partner Notification

According to the Report of the Spanish Digital Society, 2017, 86% of the youngsters aged 15 to 24 years own a smartphone, and this has become their main means of communication. It is expected that in 2018, 50% of these youngsters will exclusively use smartphones to be on the Web [14]. In addition, these youngsters are heavy users of smartphone apps. Making available a responsive smartphone app that helps to do partner notification, either personally or anonymously, may increase partner notification practice. New and innovative ways of addressing partner notification in a sustainable way that can benefit youngsters and reduce transmission are a high priority. That is why we proposed the development of a smartphone app in Spanish and in Catalan (see Figure 1 for app icon in Spanish). Experts in gamification and Web app contributed to its development, drawing on the gamification-information- motivation-behavioral skills approach to behavioral change [15].

A total of 3 workshops with youngsters of different social levels were conducted by a psychologist, anthropologists, and nurses to identify the best way to design the game.

The app contains different story games that are sensitive to sexual orientation of youngsters, adapted information to the STI that was diagnosed to the patient, and choice of different methods to do partner notification (short message service, email, WhatsApp, or face to face), either anonymously or by identifying himself or herself. At the end of the game, the youngsters will have learned preventive features of the infection, and they should be motivated to inform all sexual partners exposed to the STI; in addition, they will choose a method to send them the message or inform them personally.

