### Main Outcome Variable

The main outcome variable of the study is the percentage of partners informed of their exposure to a STI from their index cases, according to the assigned study group.

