### Control Group

The control group receives usual partner notification advice, and the health professional prints as many partner notification paper cards as the patient index case mentions to be able to provide partner notification paper cards to exposed partners. Therefore, exposed partners are expected to receive a partner notification paper card and a letter that are to be given to their health professional. The letter informs of the potential diagnosis and advised treatment. The card has information of the STI and the list of Sexual and Reproductive Health Centers and primary health care centers for sexual and reproductive health, where the recipient of the notification can go for diagnosis and potential treatment.

The random code given to the index case patient appears in the informed consent and in a short paper questionnaire (12 questions). Each 1 of the partner notification paper cards has a code in line with the study arm of the index case. This means that partners receiving a partner notification paper card from an index case assigned to the control arm are kept in the control arm themselves.

**Table 1 table1:** Sample size distribution for each primary health care center for sexual and reproductive health.

Location of health care centres^a^	Control^b^ N1	Intervention game^c^ N2	Intervention Web^d^ N3	Total N
Badalona	30	26	26	82
Sabadell	27	24	24	76
Granollers	27	24	24	74
Mollet	20	18	18	57
Mataró	20	17	17	55
Santa Coloma	14	13	13	40
Cerdanyola	12	11	11	34
Total	150	133	133	416

^a^Primary Health Care Centres for Sexual and Reproductive Health.

^b^Control group.

^c^Game intervention group.

^d^Web app direct intervention group.

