### Web App Game Intervention Group

Individuals assigned to this group receive an Information sheet explaining the objectives and procedures of the study. After providing a signature of their informed consent, they receive a paper copy of this informed consent that has a specific code through which they enter the game by connecting to the *Notijoves* Web address. A paper card with the “Notijoves” Web address is given to the patients. Once they enter the Web app, they are asked to feed the given code into the field of Young PANDORA screen.

By entering the code, they start playing the game, and they are directed through different screens and situations. A Web-based questionnaire is inserted in the game. At the end of the game, they are also asked to respond to a satisfaction questionnaire.

The game is expected to motivate the youngster to notify partners of their exposure to an STI. While playing the game, the youngsters are asked to answer questions related to the clinical symptoms, prevention, and control of their recently diagnosed STI. Like this, they *learn by playing.* Another feature of the Web app is the link to advisory videos on how to approach the *face-to-face* notification of exposure to an STI. Finally, the game ends with a screen, where the youngsters can choose from among the different electronic tools to notify (short message service, email, or WhatsApp) either anonymously or by identifying themselves.

The electronic partner notification card has the following: (1) a code automatically assigned by the electronic system that is concordant with the arm where the index case patient entered the study, (2) the informative message advising the partner to visit a health center for diagnosis and potential treatment, and (3) a link to a list of health centers of the study and the Web app address, where the partner could go and where the informed partner could enter and participate in the study by introducing the code. Along with the notification card, the partner receives an electronic letter to be given to the health professional for him to be aware of the STI diagnosed to the sender of this notification and the advised treatment.

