### What Happens to the Partners Receiving the Notification Card?

Partners visiting participating centers are easily linked to the study by their code, and they are also offered participation to the study. Once accepted, they also sign the informed consent, and they are asked to respond to a recipients’ questionnaire. After receiving the test results, if they are infected, they initiate the same procedure as an index case, with their given code, in concordance with the branch of the study that their index case was assigned. If they are not infected, the health professional registers results linked to the receptors questionnaire.

There may be partners visiting participating centers but not bringing the letter for the health professional and not having the code. These partners cannot be linked to any partner notification card, and therefore they are lost to follow-up for the system. Nevertheless, if they turn out to be infected, they are recruited as new index cases, with a new randomly assigned code. Moreover, those partners visiting a center out of the study area are lost to follow-up for the study.

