The questionnaire given to index cases collects data on the recruiting health care center, date of interview, date of birth, sex (boy, girl, transgender born as man, and transgender born as woman), country of birth, mother’s country of birth, education (without studies, primary studies, secondary studies, and university), with whom they have sex (boys, girls, or indistinctly boys or girls), number of sexual partners 6 months before the diagnosis, whether they look at webpages to obtain information about STIs (yes, no), whether they look for partners on the Web (yes, no), currently diagnosed with STI, positioning toward partner notification (will inform all partners, only some, none, and do not know), and reasons for not notifying.The questionnaire given to recipients of a partner notification card collects the same data as above and substitutes the last 3 questions with to which STI have you been exposed? How did you get to know your exposure (face to face, partner notification card, WhatsApp, short message service, email, and other)? Did you receive the notification anonymously (yes, no)?Those not wanting to participate are asked about their reasons in an open question. They are also recorded as index case or recipient of a notification.The opinion or satisfaction questionnaire collects data on whether the Web app helped its users to solve doubts related to STIs (not at all, a few, normal, quite a lot, and a lot), usefulness of the Web app to notify partners (not at all, a few, normal, quite a lot, and a lot), use of the anonymous option to notify (yes, no), easiness to choose from among the options to notify (yes, no, and if not, why not?), wish to recommend the Web app to friends (yes, no, and if not, why not?), and how can we improve the Web app? (open question)

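### Partner notification is captured by different routes in the control and web arms, and two sections disagree on which arms lose out-of-area partners, so the primary comparison can be biased without any true effect

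*Protocol article*

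**What the plan says.** The Protocol article, Main Outcome Variable, defines the outcome as the "percentage of partners informed of their exposure to a STI from their index cases, according to the assigned study group". It names no record that establishes that a partner was informed.

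The routes by which a notification becomes visible are described separately:

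- **Control.** Under Control Group, "exposed partners are expected to receive a partner notification paper card and a letter that are to be given to their health professional". The card lists centres; no online entry is described for it. The section on what happens to partners adds that a partner who attends without the letter and code cannot be linked.
- **Web arms.** Under Web App Game Intervention Group, the electronic card carries a code assigned by the system and gives the app address, "where the informed partner could enter and participate in the study by introducing the code". The section on the direct-notification arm offers the same electronic tools without describing the card again.
- **Index cases.** The only notification item for index cases, apart from reasons for not notifying, concerns intention: "positioning toward partner notification (will inform all partners, only some, none, and do not know". No later report of who was informed is described.
- **Face to face.** The app development section says the app offers a "choice of different methods to do partner notification (short message service, email, WhatsApp, or face to face".

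On partners who attend elsewhere, the section on partners receiving the card says "those partners visiting a center out of the study area are lost to follow-up for the study", without naming an arm. The Limitations section says partners "visiting a health center out of the study area will be lost to follow-up if they are assigned to the control group", and that this overestimates notification yield in the other arms. It adds that malicious anonymous use of the app may also inflate yield.

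**The concern.** Randomisation balances the index cases. It does not balance how the outcome is observed. If a control notification is seen only when a partner attends with a card, while a web notification can be seen without a visit, then equal true notification gives unequal recorded notification. The difference would look like a treatment effect.

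The Data Analysis section would not remove it. Adjustment for confounders does not address outcome measurement. Multiple imputation needs a value to be recognised as missing, and an unreturned control card looks the same as a partner who was never told.

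The primary hypothesis is at stake. The Conclusions contemplate use throughout Catalonia if the app is shown to be effective. A positive result under arm-dependent capture could not be separated from better recording in the web arms.

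**Working it through.** **The plan's own figures.** From Sample Size: 120/(1 − 0.10) = 133.3, stated as 133; 120/(1 − 0.20) = 150; 133 + 133 + 150 = 416, as stated. Bonferroni: 0.05/3 = 0.0167, stated as .016. The 120 cannot be derived, since no event rate, effect size or power is given.

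**The conflicting statements.** Take a partner in a web arm who attends outside the study area. Under the section on partners receiving the card, that partner is lost. Under Limitations, loss is tied to the control group, and the stated consequence (overestimation in the other arms) makes sense only if the web-arm partner is still counted without a visit to a study centre. Both cannot govern the same numerator.

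**Illustration of size.** The documents give no capture rates, so the following are assumptions.

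- p = true proportion informed, equal in both arms (no effect).
- c_w and c_c = share of true notifications that are recorded in web and control.
- Recorded proportions: p·c_w and p·c_c. Apparent RR = c_w/c_c.
- n = 120 per arm, one independent binary unit per evaluable index case; pooled z-test, two-sided .016, z = 2.409.
- Probability of a false result favouring web = 1 − Φ((z·s0 − d)/s1), where d is the difference in recorded proportions, s0 its pooled and s1 its unpooled standard error.

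Worked example, p = 60%, c_w = 1, c_c = 0.7: recorded 60% v 42%, d = 0.18, pooled proportion 0.51. Then s0 = √(0.51 × 0.49 × 2/120) = 0.0645 and s1 = √((0.60 × 0.40 + 0.42 × 0.58)/120) = 0.0635. The threshold is 2.409 × 0.0645 = 0.155, (0.155 − 0.18)/0.0635 = −0.39, and the probability is 0.65.

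| p | c_w | c_c | Recorded web v control | RR | False result favouring web, .016 |
|---|---|---|---|---|---|
| 60% | 1.0 | 0.7 | 60% v 42% | 1.43 | 65% |
| 60% | 1.0 | 0.5 | 60% v 30% | 2.00 | 99% |
| 60% | 1.0 | 0.3 | 60% v 18% | 3.33 | >99% |
| 60% | 0.8 | 0.7 | 48% v 42% | 1.14 | 7% |
| 60% | 0.7 | 0.7 | 42% v 42% | 1.00 | 0.8% (nominal tail) |
| 50% | 1.0 | 0.8 | 50% v 40% | 1.25 | 20% |
| 50% | 0.9 | 0.7 | 45% v 35% | 1.29 | 20% |
| 50% | 0.8 | 1.0 | 40% v 50% | 0.80 | about 0%; 20% favouring control |

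The rows with c_w below 1 allow for web-arm notifications made face to face and not logged. At p = 60% and control capture 0.7, an unlogged share of 20% cuts the false-positive probability from 65% to 7%, and 30% removes the bias. At the .05 level given in Data Analysis, the 50% v 40% and 45% v 35% rows rise to 34% and 35%. Equal capture at any level restores the nominal rate.

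**The case against.** The strongest reply is that the article never says app sends count as informed. The section on partners receiving the card describes one linkage route, attendance with a code, with no arm restriction. A condensed article may leave the exact numerator to the full protocol or analysis plan. A reader might infer that the trial will compare messages sent in the web arms with card-carrying attendances in the control arm. The documents do not state this, and that part of the objection stands. What remains does not depend on it: the linkage routes differ by arm, the two sections conflict, and the authors concede a direction. An analysis plan cannot recover control notifications that were never collected.

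Second, common records exist. The recipients' questionnaire asks in every arm how exposure became known, including face to face, and the number of control cards printed can be counted. This is correct. But the questionnaire reaches only partners who are already linked and take part, and printing a card informs nobody.

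Third, the bias may run the other way. Unlogged face-to-face notification by web users, and controls who see the app with friends, would both lower the apparent web advantage. This stands too. A reader might infer from the Limitations section that the net bias must favour web; the documents support that direction only for out-of-area loss and malicious use.

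**Conclusion.** The concern holds as a matter of arm-dependent capture plus an internal contradiction. The linkage routes described for the primary outcome differ between control and web, no correction is described, and the sections on partners receiving the card and on Limitations must be reconciled. Followed as written, the plan can bias its only primary comparison.

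The size cannot be determined from the documents. Under a true null, the chance of a false result favouring web at .016 runs from the nominal 0.8% to above 95%. If web capture is the lower one, the error favours control. These figures rest on assumed capture rates and on 120 independent binary units per arm, and they ignore clustering of partners within index cases. The distortion itself does not depend on sample size: a larger trial would estimate the wrong contrast more precisely. It should be settled before any comparison of outcomes by arm.

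**What to change.** State one ascertainment rule and apply it identically in all three arms. The numerator is partners linked by code at a participating centre within the same fixed window after the index case's enrolment. The denominator is the partners that the index case declared at enrolment. Base the between-arm comparison on this measure.

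- Reword the sections on partners receiving the card and on Limitations so that both apply this rule, with out-of-area loss the same in every arm.
- Report app-logged sends and online code entries only as process measures.
- Use the recipients' questionnaire to describe the route of notification.
- Do not print the app address on control cards. It would direct control partners to the intervention site and add to the contamination that Limitations already warns of.
- Confirm that each card's code identifies the index case and distinguishes partners. Control Group says only that the code matches the study arm.

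**Cost.** Coded attendance is already collected in all arms, so the work is mainly outcome wording. The measure becomes verified notification, which is narrower and lower than all notification. It may miss web-arm partners told face to face who hold no code, and a paper card and a phone message may not be kept equally well. Recruitment had begun (32 had accepted by early June 2018), so the change must be dated and recorded as made after recruitment began and before any outcome comparison.

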### Conclusions

Few studies have examined the yield of partner notification among young people, especially by the use of Web apps. The *Notijoves* smartphone app is an intervention that, if shown to be effective, may be implemented for all of Catalonia.

## Abbreviations

ICT: information and communication technology
STI: sexually transmitted infection
